## Abstract

**Background:**

Balance impairments, that lead to falls, are one of the main symptoms of Parkinson’s disease (PD). Telerehabilitation is becoming more common for people with PD; however, balance is particularly challenging to assess and treat virtually. The feasibility and efficacy of virtual assessment and virtual treatment of balance in people with PD are unknown. The present study protocol has three aims: I) to determine if a virtual balance and gait assessment (instrumented L-shape mobility test) with wearable sensors can predict a gold-standard, in-person clinical assessment of balance, the Mini Balance Evaluation Systems Test (Mini-BESTest); II) to explore the effects of 12 sessions of balance telerehabilitation and unsupervised home exercises on balance, gait, executive function, and clinical scales; and III) to explore if improvements after balance telerehabilitation transfer to daily-life mobility, as measured by instrumented socks with inertial sensors worn for 7 days.

**Methods:**

The TelePD Trial is a prospective, single-center, parallel-group, single-blind, pilot, randomized, controlled trial. This trial will enroll 80 eligible people with PD. Participants will be randomized at a 1:1 ratio into receiving home-based balance exercises in either: 1) balance telerehabilitation (experimental group, *n* = 40) or 2) unsupervised exercises (control group, *n* = 40). Both groups will perform 12 sessions of exercise at home that are 60 min long. The primary outcome will be Mini-BESTest. The secondary outcomes will be upper and lower body gait metrics from a prescribed task (instrumented L-shape mobility test); daily-life mobility measures over 7 days with wearable sensors in socks, instrumented executive function tests, and clinical scales. Baseline testing and 7 days of daily-life mobility measurement will occur before and after the intervention period.

**Conclusion:**

The TelePD Trial will be the first to explore the usefulness of using wearable sensor-based measures of balance and gait remotely to assess balance, the feasibility and efficacy of balance telerehabilitation in people with PD, and the translation of balance improvements after telerehabilitation to daily-life mobility. These results will help to develop a more effective home-based balance telerehabilitation and virtual assessment that can be used remotely in people with balance impairments.

**Trial registration:**

This trial was prospectively registered on ClinicalTrials.gov (NCT05680597).

**Supplementary Information:**

The online version contains supplementary material available at 10.1186/s12883-023-03403-3.

## Introduction

During the Coronavirus disease (COVID-19) pandemic, millions of people were forced to self-isolate and halt regular exercise and clinical visits. Several studies recently highlighted the impact of the pandemic on people with Parkinson’s disease (PD), including worsening motor symptoms, mood, anxiety, and insomnia [1–3]. Self-isolation for people with PD resulted in clinical balance (Mini Balance Evaluation Systems Test [Mini-BESTest]) scores that worsened in just two months, with increased falls [3]. From (less common) pandemics to (more common) inaccessibility to specialized care, balance telerehabilitation may become an essential aspect of rehabilitation care for people with PD and it is important to fully explore the feasibility and effectiveness.

Successful balance telerehabilitation requires the ability to perform both virtual assessment and virtual treatment. Balance is particularly challenging to assess virtually because a thorough and detailed in-person balance assessment typically involves measuring performance across multiple domains of balance (e.g., anticipatory postural adjustment [APA], postural sway, trunk range of motion, and turning) and with enough challenge to evoke imbalance, but this is difficult to carry out safely with virtual visits. Previous studies have demonstrated the feasibility of virtually assessing fall-related measures such as 5 times sit-to-stand [4], 360-degree rapid-turn-test [4], and motor symptoms by the Movement Disorder Society-sponsored revision of the Unified Parkinson's Disease Rating Scale (MDS-UPDRS) part III [5, 6]. However, a modified version of the MDS-UPDRS part III that does not include rigidity and postural instability as these items can’t be assessed virtually, has been demonstrated to be generally feasible for telehealth visits in PD [5, 7, 8]. Although recent feasibility studies have assessed clinical balance (Berg Balance Scale) [9] and motor symptoms (MDS-UPDRS-III—modified) [6, 9] virtually, before and after telerehabilitation, to the best of our knowledge, no study has assessed multiple domains of balance virtually. To capture multiple domains of balance and gait in one test, we used the Instrumented Stand and Walk Test (ISAW), a short balance and gait task, using wearable inertial sensors [10, 11]. The ISAW test results in metrics from different domains of mobility: postural sway in quiet stance, APA associated with step initiation, quality of turning 180°, and gait characteristics, that have been shown to be independent such as spatial, temporal, and upper body [12, 13]. Thus, it may be feasible to use similar task with wearable inertial sensors during a virtual visit to assess balance and gait using an instrumented L-shape mobility test. In this study, we hypothesize that a virtual visit exam using wearable sensors to quantify balance and gait during a prescribed standing, walking, and turning task (instrumented L-shape mobility test) will predict a gold-standard, in-person assessment of balance (Mini-BESTest).

Although telerehabilitation is becoming more common for people with PD, it remains to be seen whether it is feasible and efficacious for improving balance control [1, 14–17]. One recent systematic review and meta-analysis of randomized controlled trials investigated the effects of home-based virtual reality training and telerehabilitation compared to conventional therapy on balance in people with PD, multiple sclerosis, and stroke [18]. This systematic review and meta-analysis found similar effects of both interventions on balance, which was only assessed by the Berg Balance Scale. Another recent systematic review [19], highlighted the need for high-quality studies of telerehabilitation in PD. Only four studies aimed to explore the effects of telerehabilitation with clinical balance tests, such as the Berg Balance Scale [20, 21], the Activities-specific Balance Confidence scale [21, 22], and Balance Evaluation Systems Test [23]. Of these, only one was a randomized controlled trial that used supervised telerehabilitation in real-time with home-based virtual reality in people with mild-to-moderate PD [21], while the other studies were a case report [22], telerehabilitation without real-time supervision and not home-based [23], and virtual reality delivered in the clinic and at home [20]. Currently, most of the studies have used virtual reality in the telerehabilitation program [18, 19]; however, telerehabilitation in real-time, via videoconferencing, is considered a basic technology [24, 25] and potentially more accessible than virtual reality. In addition, the Clinical Practice Guideline’s recommendation for telerehabilitation is only moderate, while the recommendation for other more established approaches such as balance training, gait training, and task-specific training is high [26]. Thus far, clinical trials of home-based balance telerehabilitation via videoconferencing, supervised in real-time for people with PD are scarce.

Balance telerehabilitation for neurologic patients lacks strong evidence-based trials and it presents unique safety concerns [14] since we need to determine how patients can practice balance exercises in the home during a virtual therapy intervention with minimal risk for falls. There has been great progress in the past decade with regard to implementing motor learning and task specificity for optimal results for balance training [27]. The recent Clinical Practice Guideline recommends implementing aspects of task specificity that target specific impairments in PD such as APA, sensory integration, and challenging gait to improve balance in people with PD [26]. At this point, it is unknown if these Clinical Practice Guideline recommendations can be safely and effectively implemented in a virtual visit setting.

How an exercise program is delivered is important. We previously compared the Agility Boot Camp (ABC) exercise intervention executed via one-on-one, delivery with the physical therapist in the clinic versus at-home, unsupervised exercises (standard of care) [28]. The ABC framework targeted the underlying constraints on balance in people with PD including rigidity, bradykinesia, freezing, inflexible program selection (segmental coordination), impaired sensory integration, and reduced executive function and attention. Not surprisingly, the one-on-one, in-clinic delivery of the ABC program improved balance better than unsupervised at-home ABC [28]. We found that the Mini-BESTest had a large improvement (effect size = 0.86) after 12 sessions of in-person ABC rehabilitation and only a moderate improvement (effect size = 0.67) in the unsupervised, home exercise group [28]. In fact, the unsupervised home group improved very little across all outcome measures, while the in-person group improved the most on function and balance measures [28]. In the current study, we will adapt our original ABC program, designed to target underlying constraints on balance, to be performed virtually with appropriate safety modifications. We hypothesize that a virtual delivery of the ABC exercise program, called Tele-ABC, will be more effective than the unsupervised-ABC program in improving balance. In addition, we will explore the role of cognition, both as a potentially important covariate for successful participation in telerehabilitation and as an outcome measure after rehabilitation since executive and visuospatial functions are linked to balance [29–32], and are very important to daily-life mobility in PD. The Tele-ABC exercise program also uses embedded balance and cognitive exercises simultaneously which may improve cognition of people with PD.

Another major focus in rehabilitation care is the advancement of using objective measures to quantify movement. Our group [33] and others [34, 35] have demonstrated that objective measures of balance and mobility are more sensitive to change compared to standard clinical measures after rehabilitation. Also, we know that the assessment of mobility in the clinic may not adequately reflect mobility during daily life, accurate measurements of walking and turning in daily life represent a technical challenge from both an algorithm standpoint and the storage of the large amount of data generated [36]. We recently demonstrated that quality, but not quantity, particularly turning and foot-strike angle, in daily life, is impaired in people with PD compared to similar age control participants [37, 38]. Here we will use wearable sensors worn during daily life to measure if Tele-ABC improves mobility in every day life. We hypothesize that gait quality measured during daily life will improve after balance telerehabilitation.

The present trial has three aims: I) *virtual assessment*: to determine if a virtual balance assessment (instrumented L-shape mobility test) with wearable sensors can predict a gold-standard clinical in-person assessment of balance, the Mini-BESTest; II) *virtual rehabilitation at home*: to explore the effects of 12 sessions of Tele-ABC (experimental group) and unsupervised-ABC (control group) on balance, gait, instrumented executive function tests, and clinical scales; and III) *home monitoring after telerehabiliation*: to explore if improvements after balance telerehabilitation transfer to daily-life mobility, measured by wearing instrumented socks for 7 days.

## Methods

### Trial design

The Telerehabilitation Parkinson’s Disease (TelePD) Trial is a prospective, single-center, parallel-group, single-blind, controlled, randomized pilot trial. The study was approved by the Institutional Review Board at Oregon Health & Science University (OHSU) (eIRB #24,453) and will be conducted in accordance with the Declaration of Helsinki. This trial was prospectively registered on ClinicalTrials.gov (NCT05680597). This protocol paper follows the SPIRIT (Standard Protocol Items: Recommendations for Interventional Trials) 2013 statement and guidelines. The study design is depicted in Fig. 1.

**Fig. 1 Fig1:**
[figure not shown]
Study design. Abbreviation: ABC, Agility Boot Camp program

### Participants and eligibility criteria

The target population for this study is people with PD who meet the following inclusion criteria for all aims of this trial: 1) diagnosis of idiopathic PD from a movement disorders neurologist with the United Kingdom Brain Bank criteria of bradykinesia and one or more of the following—resting tremor, rigidity, and balance problems not from visual, vestibular, cerebellar or proprioceptive conditions; 2) responsive to levodopa (self-reported); 3) Hoehn & Yahr stages I-III; 4) ages 55–85 years old; 5) ability to follow directions in order to participate in testing procedures and exercise sessions, 6) free of any medical conditions or medication that contraindicates participation in an exercise program and 7) willing and able to participate in 12 sessions of rehabilitation intervention while also refraining from changes to other exercise programs and medications during the study period, within reason.

Exclusion criteria are: 1) major musculoskeletal or neurological disorders, structural brain disease, epilepsy, acute illness or health history, other than PD, significantly affecting gait and balance (i.e., musculoskeletal disorder, vestibular problem, head injury, stroke, cardiac disease, etc.); 2) a medical condition that precludes exercise; 3) cognitive inability to participate in an exercise program, such as Montreal Cognitive Assessment score less than or equal to 19 [39], prior diagnosis of dementia or inability to follow directions, 4) recurrent fallers, defined as more than 3 falls per week (from the patient and caregiver recollection), 5) excessive use of alcohol or recreational drugs; 6) recent change in medication; 7) inability to stand and walk for instrumented L-shape mobility test.

### Recruitment, randomization, and allocation

Subjects will be recruited from the OHSU Movement Disorders Clinic, the OHSU Parkinson Center of Oregon and Movement Disorders clinical program, the Balance Disorders Laboratory, the Oregon Clinical & Translational Research Institute, local neurologists (at Portland Metro area hospitals and clinics), community recruitment (e.g., public talks and distribute study flyers at various community outreach events and locations, such as the Senior Living Centers, Athletic Clubs, Rotary Clubs, Parkinson Support groups).

This trial will enroll 80 eligible people with PD who will be randomized at a 1:1 ratio into the experimental group (*n* = 40) or control group (*n* = 40). Both groups will perform 12 sessions of exercise at home, with each session lasting 60 min, over approximately 4 weeks. Within 24 h after baseline testing the participant will be randomized using an online module in the Research Electronic Data Capture system (REDCap). The participant will learn their random group assignment after both enrollment and the baseline testing. The randomization module in REDCap allows the randomization of participants based on the Hoehn & Yahr stage. The module also monitors the overall allocation progress and assignment of randomized subjects. We used a stratified randomized block design to allocate participants to the either experimental or control group. Randomization to arms is balanced 1:1 for each stratum, Hoehn & Yahr I and II, and Hoehn & Yahr III, respectively. We additionally used randomly permutated blocks of 2, 4, and 6 in order to keep the randomization scheme blinded to the blinded research team members to help avoid selection bias. All subjects will agree not to change their exercise activities or antiparkinsonian medication during the duration of the study, unless necessary.

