### Blinding

Due to the nature of the intervention, participants and physical therapists cannot be blinded to group allocation. However, participants will be blinded to the expected outcomes, unaware of the study hypotheses, and will be explicitly instructed not to discuss their training program with the assessors to maintain assessor blinding. A trained assessor who is blinded to group allocation will be responsible for all outcome assessments. Data analysts and statisticians will also be blinded to group allocation.

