### Assessment procedures

The pre-screening for inclusion/exclusion criteria will be done over the phone. All assessments will take place at the participant’s home and/or virtually. Immediately after the home and virtual assessments at baseline, participants will complete 7 days of daily-life mobility monitoring and then start the 12 intervention sessions (experimental or control). Following the 12 sessions, participants will complete post-testing repeating the home and virtual assessments and daily-life monitoring for 7 days. An overview of the study assessments is detailed in Table 3. All the participants will be assessed at the same time of day and in the clinically defined ‘‘on’’ state (fully medicated).

**Table 3 Tab3:** Overview of the study assessments and intervention period

Outcome Assessments	Pre-exercise: Home Visit	Pre-exercise: Virtual Visit	Pre-exercise: 7 days of Sensors During Daily Life	12 sessions of exercise intervention	Post-exercise: Home Visit	Post-exercise: Virtual Visit	Post-exercise: 7 days of Sensors During Daily Life
Mini-BESTest *(primary outcome)*	X				X		
Instrumented L-shape mobility test with wearable sensors		X				X	
ISAW with wearable sensors	X				X		
Daily-life mobility with instrumented socks and wearable sensor			X				X
MDS-UPDRS	X				X		
ABC	X				X		
PDQ-39	X				X		
NFoGQ	X				X		
FES-I	X				X		
IPAQ	X				X		
5 times sit-to-stand task	X	X			X	X	
360-degree Turn Test (right and left)	X	X			X	X	
Floor Transfer Test	X				X		
Self-Efficacy for Exercise	X				X		
Life-Space Questionnaire	X				X		
TSS					X		
HEP					X		
TabCAT	X				X		
Timed-up-and-go test		X				X	
Self-perceived Mini-BESTest		X					
PGIC					X		

*Abbreviations*: *Mini-BESTest* Mini Balance Evaluation Systems Test, *ISAW* Instrumented Stand and Walk Test, *MDS*-*UPDRS* Movement Disorder Society-Sponsored Revision of the Unified Parkinson’s Disease Rating Scale, *ABC* Activities-Specific Balance Confidence, *PDQ-39* Parkinson’s Disease Questionaire-39, *NfoGQ* New Freezing of Gait Questionnaire, *FES-I* Falls Efficacy Scale-International, *IPAQ* International Physical Activity Questionnaire- Short Form, *TSS* Telerehabilitation Satisfaction Scale, *HEP* Home Exercise Program, *PGIC* Patient Global Impression of Change, *TabCAT* Tablet-based Cognitive Assessment Tool

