#### Aim III

To determine if daily-life mobility changes after interventions, our main analysis will be the paired t-tests to compare the values in each metric described in Table 4 in the pre and post-exercises, separately. We will use the same statistical procedures as described in Aim II to explore improvement (estimated) between groups since no study has investigated the effects of any intervention on daily-life mobility using instrumented socks with wearable sensors.

Missing data: We will first assess the missing data frequency and patterns for both primary outcomes. If ≤ 5% of observations are missing the primary outcome, then multiple imputation methods will not be of benefit and we will perform analysis without imputation. If > 5% of observations are missing outcomes, we will perform multiple imputations as necessary to address the missing-ness. For all analyses, level of significance will be set at *p* ≤ 0.05.

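### The article does not secure the Aim III baseline sensor week ahead of randomisation and disclosure of the arm; read naturally, most of that week falls after randomisation

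*Protocol article*

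**What the plan says.** Four places in the protocol article bear on the order of events.

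- *Recruitment, randomization, and allocation*: "Within 24 h after baseline testing the participant will be randomized using an online module". On disclosure: "The participant will learn their random group assignment after both enrollment and the baseline testing". Neither sentence defines baseline testing or mentions the sensor week.
- *Assessment procedures*: "Immediately after the home and virtual assessments at baseline, participants will complete 7 days of daily-life mobility monitoring and then start the 12 intervention sessions".
- *Abstract, Methods*: "Baseline testing and 7 days of daily-life mobility measurement will occur before and after the intervention period". Baseline testing and the sensor week appear here as two items.
- *Blinding*: "participants and physical therapists cannot be blinded to group allocation", although "participants will be blinded to the expected outcomes, unaware of the study hypotheses".

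The sensor week supplies the pre value for Aim III. Under *Statistical analysis, Aim III*, "our main analysis will be the paired t-tests to compare the values in each metric described in Table 4", before and after exercise. The Aim II procedures (mixed model, ANCOVA on change, t-test on change) are then used to explore differences between the groups.

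**The concern.** A baseline used to measure change should be complete before the participant can react to the allocation. If the 24-hour clock for randomisation starts at the end of the home and virtual visits, it runs out while the sensor week has barely begun. A participant who then learns the arm spends most of the baseline week knowing it.

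Gait speed, stride length, turning and wear in daily life are things a person can alter, deliberately or not. A change made in response to the allocation would move the pre value itself, and every planned Aim III analysis uses that value. Aim III is meant to supply effect sizes for planning a larger trial, so an error here would carry forward. Anyone who withdraws on learning the arm during that week would also leave an incomplete Aim III baseline.

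**Working it through.** **Step 1. Order of events under each reading of baseline testing.**

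| Reading | Randomisation | Sensor week | Consequence for Aim III |
|---|---|---|---|
| Home and virtual visits only | within 24 h of the last visit, about day 0 to 1 of the week | about six of seven days after randomisation | pre value largely post-randomisation; unblinded if the arm is disclosed promptly |
| Visits plus the sensor week | after day 7 | entirely before randomisation | no problem |

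*Evidence for the first reading.* The abstract names the two items separately. *Assessment procedures* starts the week immediately after the visits and ties the word baseline to the visits. *Daily-life monitoring* has the sensors mailed back or collected after the week, so a 24-hour rule fits a staffed visit better than the end of an unattended week.

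*Evidence for the second.* *Assessment procedures* describes post-testing in a way that can include the sensor week, so baseline testing might include it by symmetry. Table 3 lists the week among the pre-exercise assessments.

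The first reading is the more natural, but the text does not settle it. The study design figure (Fig. 1) was not available for this check.

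**Step 2. Disclosure.** The article gives only the earliest time: after enrolment and baseline testing. Under the first reading, disclosure may fall before, during or after the sensor week.

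**Step 3. The plan's own figure.** Aim III states at least 80% power for a paired t-test with d = 0.45, n = 40 and alpha 0.05 (sidedness not stated). Two-sided noncentral t: df = 39, ncp = 0.45 × √40 = 2.85, power 79.3%. The normal approximation gives 81.2%. The stated figure is reproduced; it does not depend on the order of events.

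**Step 4. What a reaction to allocation would do (illustration).** The documents give no size for such a reaction. Assume that knowing the arm shifts the baseline-week mean by b, in SDs of the pre/post change, and take b from 0 to 0.20.

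- Paired test, shift towards improvement: the apparent effect is 0.45 − b, so ncp = (0.45 − b) × √40.
- Paired test, no true change: ncp = b × √40 in absolute value.
- Between-arm t-test on change, 40 per arm, shift in one arm only, no true difference: df = 78, ncp = b / √(2/40).

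| b | Paired power at true d = 0.45 | Paired type I error | Between-arm type I error |
|---|---|---|---|
| 0 | 79% | 5.0% | 5.0% |
| 0.05 | 69% | 6.1% | 5.6% |
| 0.10 | 58% | 9.5% | 7.3% |
| 0.20 | 34% | 23.5% | 14.3% |

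A shift in the opposite direction would exaggerate the pre/post change instead. An equal shift in both arms would leave the between-arm contrast intact but still distort each arm's paired test. With b = 0 nothing changes.

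**The case against.** The strongest reply is that an undefined term is being read in the unfavourable way. The abstract sentence is loose (it has baseline testing occurring after the intervention as well as before it), and the article's description of post-testing supports the inclusive reading. This stands to the extent that the post-randomisation order cannot be asserted as fact.

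A reader might also infer that participants are told their arm before the week starts. The article does not say so, and randomisation without disclosure to the participant or therapist gives participants nothing to react to.

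A reader might go further and conclude that the Aim III change is biased. The documents show a risk only. No exercise session takes place before the week ends, both arms receive identical exercises, participants are unaware of the hypotheses and agree not to change their exercise activities, daily wear time is prescribed, and the five main metrics describe gait quality rather than amount of activity. These features make a large reaction less likely. They do not exclude one, because hiding the hypotheses does not hide the arm, and passive sensors do not stop people from moving differently.

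Two further inferences also fail:

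- It would be wrong to say that no analysis could help. A between-arm comparison of post values, adjusted only for variables measured before randomisation, avoids the affected week. It is not among the stated Aim III analyses, however, and it cannot rescue the paired tests that are the main one.
- An assumed between-arm shift in raw SDs cannot be expressed as a share of 0.45, because that figure is a within-arm paired effect on a different scale.

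Finally, this is a pilot trial and Aim III yields preliminary estimates. That limits the severity, but those estimates are meant to inform the size of a later trial.

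**Conclusion.** The concern holds for Aim III in a limited form. The article's timing statements, read together, most naturally place about six of the seven baseline sensor days after randomisation, and they permit disclosure of the arm before or during that week. The opposite order is possible but nothing in the text secures it. On the natural reading, with early disclosure, the paired pre/post and between-group Aim III estimates are open to bias of unknown direction and size.

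The illustrative figures rest wholly on an assumed shift: at 0.05 SD of the change the effect on error rates is slight, and at 0.20 it is serious. They show sensitivity and are not a forecast.

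The Mini-BESTest primary outcome and the other home and virtual visit baselines precede randomisation on either reading and are not affected. This should be fixed, for Aim III only.

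**What to change.** In *Recruitment, randomization, and allocation*, define baseline as the home visit, the virtual visit and the completed 7-day monitoring. State that REDCap randomisation takes place only after the seventh monitoring day and before session 1. If randomisation must come earlier for practical reasons, then at the least withhold the arm from both participant and therapist until the seventh day is over. Bring the abstract and *Assessment procedures* into line with that definition, and make the end of monitoring a condition for opening the randomisation module.

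If anyone has already been randomised in the other order, state the limitation for the Aim III pre/post and between-group results.

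Cost: one sentence in the protocol, matching wording in two other places, and a change of form order in REDCap. The downside is slightly less lead time to book the first session.
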